### Adverse events and risk management

During the general psychotherapy training and especially during the CBASP@YoungAge Workshop, study therapists are prepared for unexpected and adverse events. In case of such an event during the CBASP@YoungAge intervention, the study coordination (ND) is informed immediately, and (serious) adverse events are reported to the entire study team (HC, ELB). Detailed information on the definition of (serious) adverse events and detailed documentation procedure within the study can be found in Additional file 3. The initiation of pharmacological treatment during study therapy in the intervention group is also reported to the study coordinator (ND). The dose, duration, and type of medication are documented. In the TAU control group, medication can be part of the standard treatment course.

Individuals with depression carry a higher risk of self-harm and suicide than the general population. Thus, all trial participants are monitored by their responsible outpatient clinic. In the case of patients with an increased risk of acute suicidal tendencies, regular explorations are carried out by the appropriately trained study therapists. In case of uncertainty, an experienced therapist on duty is called in. This represents the standard procedure of the outpatient clinics and thus also of the study. It includes regular consultation with the outpatient clinic management and responsible supervisors of the study therapists. Participants will be able to contact the study coordinator (ND) during the trial period until the end of the follow up assessment.

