**Method:**

This quasi-experimental pilot feasibility trial is a phase 1 to phase 2 study investigating the feasibility and effectiveness of CBASP@YoungAge by including an intervention group (CBASP@YoungAge) and a treatment-as-usual control group. The treatment of depressive symptoms as well as interpersonal problems with primary caregivers are the main targets of CBASP@YoungAge. Personalization is ensured concerning the treatment course, caregivers’ involvement, and the patient’s age. The primary outcome relates to two areas: the feasibility of the CBASP@YoungAge treatment program in an outpatient context and a change in patients' depressive symptomatology from before to after treatment. We conduct a brief process evaluation after each session in the intervention group to closely monitor the treatment process and examine feasibility from the therapists' and patients' perspectives and mechanisms of symptom change. In addition, we consider interpersonal behavior between children and caregivers, parenting behavior, and monitor the global-health-index in children and parents as secondary outcomes. Pre-, post-, and follow-up data are evaluated.

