**Fig. 2 Fig2:**

Timeline of the study

The psychotherapeutic process is evaluated during treatment by the study therapists. If difficulties arise during treatment, the study therapists contact the study team in the appropriate outpatient clinic. The intervention or follow-up is discontinued if the caregivers or patients withdraw consent or a different treatment becomes necessary. The therapy process is also discontinued if the trial has to be unexpectedly canceled, or if the study coordinator decides it is necessary to discontinue, for example in case of adverse events. The risk management information below provides further information. The date and reason for discontinuation or drop-outs after screening will be documented.

After treatment completion, trained therapists will carry out regular post-assessments who were not involved in the treatment. Participants have to wait for at least 6 weeks before booster sessions are allowed when needed. If follow-up treatment (e.g., for comorbidities) appears to be necessary during booster sessions, that can be implemented as part of regular outpatient treatment, and will be documented (see Fig. 3 for the study flow).

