#### Therapy process evaluation

An evaluation is implemented for continuous therapy support by relying on the MRC guidance [75] on how to conduct process evaluations of interventions. This consists of short questionnaires to be completed by everyone involved after each therapy session, and of short questionnaires (KIDSCREEN-10, PMH) after every fifth therapy session. As the study’s target population are youth patients with depression and stressful family relationships, process evaluation is as short and practicable as possible. We therefore limit ourselves to documenting the change in symptoms compared to the beginning of therapy (subjective rating of 1 = “worse” to 10 = “better”), the satisfaction with the actual therapy session (subjective rating 1 = “dissatisfied” to 10 = “satisfied”) and ask for qualitative descriptions of other comments. These open-ended questions are not intended to be a substitute for careful qualitative analysis, but allow us to capture unanticipated therapy events from the participants' perspective not yet included in the protocol. The aim of this first step in the process evaluation is to check the intervention’s feasibility and establish the course of symptoms over time as well as the participants’ general health-related well-being.

In the second step, we focus specifically on the structure of each therapy session by asking therapists how they conduct each session. For that purpose, they fill out a session log sheet after each session. Here they indicate how long the session lasted, who participated, which techniques they applied, and whether the session was conducted online or face-to-face. This will help us understand the feasibility and implementation of each module and session, and optimize the program after this study.

Furthermore, we focus specifically on the intervention’s structure. Have the therapists implemented it correctly? The therapists fill out a session protocol sheet after each session for just this reason. Here they indicate the frequency and duration of the sessions, who participated, and whether the appointments were implemented online or live. This helps us better understand the feasibility and implementation of each module and to identify potential structural differences related to specific modules.

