### Statistical analysis

A preliminary analysis of the results after post-assessment is planned. A full analysis will follow the completion of all follow-up assessments. Data will be analyzed based on the Intention-to-treat (ITT) sample and will help inform power calculations for a future CBASP@YoungAge randomized control trial.

Central aspects with regard to feasibility in the analysis are attrition and reasons for drop-out of patients or parents. These aspects will be recorded and analyzed. Recruitment rate is measured by reporting the number and reasons of patients screened for the intervention group who decided against study participation. We also capture the proportion of patients who participate in each arm at pre-, post- and 6-month follow-up assessment. Furthermore, we access the proportion of patients meeting criteria for response and remission based on the Kinder-DIPS at the different time points. With regard to attrition, therapists will assess the number of sessions of the modules, and the session frequency in general and related to the different modules. In addition, we will record each participant’s individual course of therapy in self-reports, and reports from others, as well as any unexpected events in the course of therapy. For participants who withdraw from the study, the researcher will follow-up with either the therapists or participants to document their reason(s) for study withdrawal. We will assess rates and types of missing data, and the proportion of drop-outs at different stages throughout the trial. We will also assess whether any of the measures display floor and/or ceiling effects. Patient adherence to treatment will be indexed by the mean (SD) number of therapy sessions offered and attended, and by calculating the proportion of participants who undergo a minimum adequate dose (eight or more sessions) in each arm. Adherence of protocol by therapists is analyzed descriptively by the proportion of complete adherence checks and the monitoring of individual case and data management in the study routine. Data completeness is reported as proportions of missing values. Due to sample size and this study’s pilot character, the feasibility analysis is mainly based on the intervention group’s process evaluation. First-interim analyses of results are only possible with sufficient post-measurements. Missing values will be integrated in an iterative imputation method based on a random forest model.

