In addition to the results in terms of clinical relevance, the practicality and feasibility of the trial are also important. Those results will allow us to evaluate the feasibility and effectiveness of this treatment program and will provide valuable information on whether this modular and interaction-focused treatment can actually be implemented in other outpatient treatment settings at different locations. In particular, its feasibility from the perspective of the patients and their relatives, as well as from the therapists will be examined. Any obstacles can be removed and necessary changes can be made according to the results. Furthermore, building on this non-randomized pilot study’s results, we will be able to plan a large controlled randomized trial. Whether this is applicable depends on various factors and aspects. Central is whether the CBASP@YoungAge treatment does not cause harm to patients or relatives. Furthermore, it is important to know whether recruitment is possible in order to implement a larger study and if the therapy can be carried out and terminated by therapists and patients with a reasonable amount of effort. Aspects that are also considered in the evaluation of feasibility are cost-effectiveness, duration of therapies and study as well as effectiveness and feasibility of data management.

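### Harm is central to the decision on an RCT, but immediate adverse-event notice and reports of started medication are written for the CBASP@YoungAge arm only

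*Protocol article*

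**What the plan says.** The Discussion lists what the step to a randomised trial depends on and puts safety first: "Central is whether the CBASP@YoungAge treatment does not cause harm to patients or relatives".

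Adverse events and risk management then sets out how events are handled. The immediate-notice rule reads "In case of such an event during the CBASP@YoungAge intervention, the study coordination" is told at once, and (serious) adverse events go on to the whole study team. The medication rule is also specific to one arm: "The initiation of pharmacological treatment during study therapy in the intervention group is also reported to the study coordinator", with dose, duration and type documented. For TAU the section says only that medication may form part of standard care. Definitions and procedure are placed elsewhere: "detailed documentation procedure within the study can be found in Additional file 3". That file is not available here.

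Several provisions name no arm:
- Under Recruitment and procedure, "If difficulties arise during treatment, the study therapists contact the study team in the appropriate outpatient clinic", and the date and reason for discontinuation are documented.
- Adverse events and risk management has all participants monitored by their own clinic and lets them contact the coordinator until follow-up ends.
- Statistical analysis records each participant's course of therapy, "as well as any unexpected events in the course of therapy".

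The open questions in the process evaluation are also meant to "allow us to capture unanticipated therapy events". Recruitment and procedure plans that evaluation without naming an arm, but the Abstract places it in one: "We conduct a brief process evaluation after each session in the intervention group".

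**The concern.** The same section notes that depressed patients carry a raised risk of self-harm and suicide. Some adverse events are therefore to be expected under any treatment, and an event count from the CBASP@YoungAge arm is hard to read without a count from TAU collected in the same way. As written, the two rules most likely to produce prompt and complete reports apply to one arm. Preparation for adverse events also comes especially from the CBASP@YoungAge workshop, which only intervention therapists attend.

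This is a stated difference between arms, not an omission that condensing a protocol into an article would explain. If it leads to less complete capture in TAU, the error has a known direction: it makes the new programme look worse than TAU, on the question the sponsor calls central.

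**Working it through.** The plan gives no event rate, capture rate or harm figure, so there is nothing to reproduce. The check is a comparison of the text, then arithmetic under stated assumptions.

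**Routes by arm, as written**

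| Route | CBASP@YoungAge | TAU |
|---|---|---|
| Immediate notice of an event to the coordinator | Stated | Not stated |
| Report of started medication | Stated | Not stated |
| Therapist contacts local study team about difficulties | Yes | Yes |
| Clinic monitoring; participant may contact coordinator | Yes | Yes |
| Discontinuation date and reason | Yes | Yes |
| Unexpected events in each course of therapy recorded | Yes | Yes |
| Session-level open questions | Yes | Unclear (Abstract: intervention group) |
| Additional file 3 definition and documentation | Referred to | Cannot be checked |

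**Effect of unequal capture.** Let p be the true proportion of patients with an event, equal in both arms (a harmless programme), and c the share of TAU events captured, with full capture under CBASP@YoungAge. The apparent risk ratio is p/(p × c) = 1/c, whatever p is. At c = 0.75 it is 1.33; at c = 0.50 it is 2.0. Both values of c are assumed.

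Expected affected patients, with the planned 22 per arm (Participants and sample size) and assumed p:

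| p | CBASP@YoungAge, 22p | TAU, c = 0.75 | TAU, c = 0.50 |
|---|---|---|---|
| 20% | 4.4 | 3.3 | 2.2 |
| 10% | 2.2 | 1.65 | 1.1 |
| 5% | 1.1 | 0.83 | 0.55 |

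**Sampling error with equal reporting.** An observed 4 of 22 has an exact 95% interval of 5.2% to 40.3%. For 4 of 22 in each arm the difference is 0, with a Newcombe 95% interval of -23 to +23 percentage points. At equal person-time the rate ratio is 1.0, with an exact conditional interval of 0.19 to 5.4. A bias of 1.33 to 2.0 lies well inside that range.

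**Length of observation.** CBASP@YoungAge has 20 to 30 sessions at one to three a week. The shortest course is 20/3 = 6.7 weeks and the longest 30/1 = 30 weeks, a 4.5-fold range. TAU has no set length. Assume a constant hazard giving 20% in 30 weeks: h = -ln(0.8)/30 per week. Then 15 weeks gives 1 - exp(-15h) = 10.6%, and 60 weeks gives 1 - exp(-60h) = 36%. Unequal observation time can therefore distort a comparison of proportions as much as unequal capture.

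**The case against.** The strongest case against has four parts.

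- **Notice is not capture.** Immediate notice governs who is told and how fast, not whether an event is counted. Closer escalation for a treatment new to this age group is a reasonable safety choice, and unexpected events are recorded for each participant without reference to arm. This stands to a large extent. A reader might infer that TAU events go unrecorded; the text does not support that. What remains is that the general routes state no matching trigger to the coordinator, so equal completeness is not secured.
- **The missing file.** Additional file 3 describes documentation within the study, not within one arm. A reader might conclude that TAU lacks the same definition or form, or that no like-for-like TAU reference exists. Neither can be said without that file. If it covers both arms, the remaining fault is the arm-limited wording of the article.
- **No between-arm comparison of harm is stated.** This is correct. The sponsor asks whether the programme causes harm, and feasibility rests mainly on the intervention group's process evaluation. The risk ratio of 1/c therefore describes how a reader would be misled when setting the counts side by side, not a bias in a planned estimate. With a raised background risk and a control arm already in place, that reading is hard to avoid.
- **The effect is hypothetical and small.** The rates are assumed, the bias is below the sampling error, and it errs towards caution. All true. The case for changing the plan is that the problem is avoidable at little cost, not that it is large.

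**Conclusion.** The point holds in limited form. As written, immediate event notice and reports of started medication apply to CBASP@YoungAge only, while harm is named as central to the next trial. If TAU events are caught less completely as a result, the intervention count lacks a fair reference, and a harmless programme could appear to carry 1.33 times the TAU risk (75% capture) or twice that risk (50% capture). Both capture shares are assumptions, as are the event rates.

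Equal reporting would not turn this into a test of harm. With 22 per arm the intervals stay wide, and arm remains confounded with clinic and calendar time, as the limitations in the Discussion largely acknowledge. The change is worth making but does not decide the value of the study. Confidence is moderate because Additional file 3 is unseen.

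**What to change.** 1. In Adverse events and risk management, replace the phrase that limits notice to the CBASP@YoungAge intervention with *during study therapy or follow-up in either arm*. Apply the Additional file 3 definition and form in all three clinics. If that file already does so, correcting the article's wording is enough.
2. Record start, dose, duration and type of medication in both arms, as a co-intervention rather than as a harm.
3. Report serious adverse events per arm descriptively, together with length of observation, because treatment length can differ between arms. State that this removes only unequal ascertainment and leaves clinic and calendar-time confounding in place. The observation window and interval method can be left to the analysis plan.
4. Show TAU events from before the change separately, as retrospective, and do not pool them with later ones.

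**Cost.** One form in the two TAU clinics, which already monitor these patients, and one descriptive table. The downside is a small reporting burden and possibly an ethics notification for those clinics. Use of earlier clinic records may need consent, and those records would be less complete. Under Trial status, control recruitment was expected to run to December 2022, so on that timetable later TAU patients could be covered prospectively.

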### Statistical analysis

A preliminary analysis of the results after post-assessment is planned. A full analysis will follow the completion of all follow-up assessments. Data will be analyzed based on the Intention-to-treat (ITT) sample and will help inform power calculations for a future CBASP@YoungAge randomized control trial.

Central aspects with regard to feasibility in the analysis are attrition and reasons for drop-out of patients or parents. These aspects will be recorded and analyzed. Recruitment rate is measured by reporting the number and reasons of patients screened for the intervention group who decided against study participation. We also capture the proportion of patients who participate in each arm at pre-, post- and 6-month follow-up assessment. Furthermore, we access the proportion of patients meeting criteria for response and remission based on the Kinder-DIPS at the different time points. With regard to attrition, therapists will assess the number of sessions of the modules, and the session frequency in general and related to the different modules. In addition, we will record each participant’s individual course of therapy in self-reports, and reports from others, as well as any unexpected events in the course of therapy. For participants who withdraw from the study, the researcher will follow-up with either the therapists or participants to document their reason(s) for study withdrawal. We will assess rates and types of missing data, and the proportion of drop-outs at different stages throughout the trial. We will also assess whether any of the measures display floor and/or ceiling effects. Patient adherence to treatment will be indexed by the mean (SD) number of therapy sessions offered and attended, and by calculating the proportion of participants who undergo a minimum adequate dose (eight or more sessions) in each arm. Adherence of protocol by therapists is analyzed descriptively by the proportion of complete adherence checks and the monitoring of individual case and data management in the study routine. Data completeness is reported as proportions of missing values. Due to sample size and this study’s pilot character, the feasibility analysis is mainly based on the intervention group’s process evaluation. First-interim analyses of results are only possible with sufficient post-measurements. Missing values will be integrated in an iterative imputation method based on a random forest model.

We intend to carry out analyses with regard to effectiveness. Summary statistics will be used as appropriate to describe and compare data for all participants. ANCOVA models will be used to test the pre- and post-differences in the intervention group and the difference between intervention and control group after the intervention and at follow up. Within or between-group effect sizes (Cohen’s *d*) will be calculated and interpreted according to standard conventions (< .50 = small; .50–.80 = medium; > .80 = large [76]).

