However, the results we expect from this pilot study are also hampered by certain limitations. Firstly, it is based on a quasi-experimental design. Since all participants in the intervention group are treated in the Marburg outpatient clinic and all TAU participants are treated in either the outpatient clinic in Bochum or Landau, no randomization is possible, which also means that study-site effects cannot be excluded. Secondly, due to the Corona pandemic, we could not start collecting data at all three outpatient clinics at the same time. That makes seasonal side effects possible between the intervention and control groups (also due to the respective pandemic situation). Third, the design is focused on assessing the feasibility of the treatment program. However, this leads to the fact that not all relevant aspects, e.g., the therapeutic alliance, can be captured. Fourth, because of the ongoing pandemic situation, we were unable to define numeric progression criteria. Regarding the various safety regulations, the rules for outpatient psychotherapy were and are frequently changed. Thus, it was not possible to predict exactly how recruitment, duration of therapy, or even data management would proceed. However, we will carefully monitor the different progression criteria to determine whether progression is feasible and to learn how to adapt and improve progression in a large-scale RCT trial.

Finally, the study’s design means that patients and therapists cannot be blinded which could create some bias among therapists and patients. However, we are trying to mitigate possible biases resulting from the lack of blinding by ensuring that the clinical evaluations are not done by us study therapists but rather by independent blinded raters. Against the background of the first investigation of this intervention within the framework of a phase 1/phase 2 clinical trial, these limitations appear in general justifiable.

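### Harm is the central condition for the later randomised trial, but the stated analysis gives no worsening rate by arm for patients or caregivers

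*Protocol article*

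**What the plan says.** In the Discussion, the article lists what decides whether a larger randomised trial follows and gives one condition the leading place: "Central is whether the CBASP@YoungAge treatment does not cause harm to patients or relatives". Among the limitations it adds that "because of the ongoing pandemic situation, we were unable to define numeric progression criteria". It explains this by unpredictable recruitment, therapy duration and data handling under changing pandemic rules.

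The Statistical analysis section names one set of patient categories: "Furthermore, we access the proportion of patients meeting criteria for response and remission based on the Kinder-DIPS at the different time points". The effectiveness analysis works on means: "ANCOVA models will be used to test the pre- and post-differences in the intervention group and the difference between intervention and control group", with Cohen's d as the effect size. The Outcomes section includes the MFQ for patients and the BSI for caregivers, but labels nothing as a harm outcome.

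Worsening is recorded in several places:

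- Therapy process evaluation: everyone involved fills in a short form after each session, "documenting the change in symptoms compared to the beginning of therapy (subjective rating of 1 = “worse” to 10 = “better". KIDSCREEN-10 and PMH follow every fifth session.
- Statistical analysis: "In addition, we will record each participant’s individual course of therapy in self-reports, and reports from others, as well as any unexpected events" are to be documented.
- Adverse events and risk management: events are passed to the study team, and "Detailed information on the definition of (serious) adverse events and detailed documentation procedure within the study can be found in Additional file 3". That file is not available here.

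For patients who withdraw, "the researcher will follow-up with either the therapists or participants to document their reason(s) for study withdrawal".

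**The concern.** The article states its own decision condition and also states which patient categories it will count, and the two do not meet. Response and remission both point in the favourable direction. On those counts a patient whose depression gets worse is a non-responder, like a patient who has not changed. ANCOVA and Cohen's d describe averages. For relatives, whom the harm condition names explicitly, no count of any kind is stated.

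The sources that do record worsening are described mainly for one arm. The abstract places the session-by-session evaluation in the intervention group. The adverse-event route is written for events during the CBASP@YoungAge intervention. The Statistical analysis section rests feasibility mainly on the intervention group's process data. Some depressed young people get worse under any treatment, so a worsening figure from one arm alone is hard to read.

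At stake is the decision to proceed: the harm condition could be judged met on a favourable average and a reading of individual reports, with no worsening rate set beside the control arm.

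**Working it through.** **1. Condition against stated analysis.**

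- Patients: the categories named are response and remission, and the continuous outcomes are compared as means. No worsening category is named.
- Relatives: BSI and PMH are collected, but no individual worsening criterion is named.
- Comparison with TAU: MFQ and BSI are T1, T2 and T3 outcomes for the trial. Session ratings and the adverse-event route are described mainly for CBASP@YoungAge. The Recruitment and procedure section mentions the session evaluation without naming an arm, so mainly is the accurate word.
- Session scale: as described, only its ends are labelled. No value is given for unchanged, so no worsening count follows from it directly.

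**2. Can a mean conceal worsening?** Assumed illustration: of 22 patients, 4 worsen by 1 SD and 18 improve by 1 SD. Mean gain = (18 × 1 − 4 × 1)/22 = 14/22 = 0.64 SD, which the article's convention (.50 to .80) calls medium.

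**3. How many patients would contribute?** Participants and sample size gives 44 recruits (22 per arm), 60% retention and 38 completers. These do not agree: 44 × 0.60 = 26.4, while 38/44 = 86.4%. I therefore carry three sizes per arm: 22 (all), 38/2 = 19, and 22 × 0.60 = 13.2, about 13.

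**4. What would zero cases of worsening show?** One-sided 95% upper limit = 1 − 0.05^(1/n); upper end of the two-sided exact 95% interval = 1 − 0.025^(1/n). The chance of at least one case is 1 − (1 − p)^n, for assumed true rates p.

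| n in the arm | One-sided limit | Two-sided limit | At least one case, p = 5% | At least one case, p = 10% |
|---|---|---|---|---|
| 22 | 12.7% | 15.4% | 68% | 90% |
| 19 | 14.6% | 17.6% | 62% | 86% |
| 13 | 20.6% | 24.7% | 49% | 75% |

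**5. Can a worsening threshold be set from the article?** Reliable change in baseline SD units = 1.96 × √2 × √(1 − alpha). Higher MFQ item scores mean more symptoms, so worsening is a rise.

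- MFQ self-report, German alpha .93: 1.96 × √2 × √0.07 = 0.73 SD.
- MFQ caregiver report, German alpha .90: 1.96 × √2 × √0.10 = 0.88 SD.
- With the US alphas that the article also gives (.89 and .91), the thresholds are 0.92 and 0.83 SD.
- BSI depressiveness, alpha .87: 1.96 × √2 × √0.13 = 1.00 SD. The BSI section gives reliabilities for scales but none for a global index, so no global threshold can be derived.

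**6. Withdrawals.** At 60% retention, 22 × 0.40 = 8.8, about 9 CBASP@YoungAge patients, would have a withdrawal reason. With 19 completers it would be 22 − 19 = 3. The stated rule allows the treating therapist to be the only source of that reason.

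**The case against.** The strongest reply is that worsening is not ignored. Patients, caregivers and therapists rate change after every session on a scale that starts at worse. Open comments are meant to catch unforeseen events, individual courses are kept, and adverse events go to the study team. This stands. A reader might infer that the plan never captures worsening, or that it relies only on spontaneous reports. The first is contradicted by the text. The second cannot be checked, because the adverse-event procedure is in Additional file 3.

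A second reply is that deterioration tables usually belong in an analysis plan or full protocol, neither of which is shown, and that the article does not exclude further counts. This also has weight, and it is why the point is confined to what the article does state: which categories are counted, which condition is central, and in which arm the harm-relevant data are described.

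Third, one might say that the Kinder-DIPS cannot show worsening because every patient has the diagnosis at entry. That goes too far. The interview covers other disorders, so new diagnoses would be visible, as would relapse between T2 and T3. What the stated counts do not separate is greater severity within the entry diagnosis.

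Fourth, a count at T2 misses those without T2 data, which the random forest imputation would fill with modelled values, and alphas from other samples may not hold here. Both are fair and shape the fix. The fix also sets no numeric harm limit; the article already discloses that it has no progression thresholds.

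**Conclusion.** The concern holds in a limited form. Absence of harm is central to the trial's next step and worsening is recorded in places, but no stated analysis turns it into a rate for patients or caregivers that can be set against TAU. The reason given for having no numeric criteria, namely uncertainty over recruitment, duration and data management, does not prevent such a count.

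A reader might conclude that the trial cannot answer its own question on harm. The documents do not support that: session ratings, individual courses and adverse-event reports are evidence. They lack a defined count and a described counterpart in the control arm. The effectiveness analyses are unaffected.

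The 0.64 SD figure is an illustration, not a forecast. Even with the count, precision is low: zero cases would leave true rates up to 12.7%, 14.6% or 20.6% compatible, depending on which retention figure applies. The comparison with TAU would be descriptive, since the arms are treated at different clinics and the article itself says that site effects cannot be excluded.

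**What to change.** In the Statistical analysis section:

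- Report by arm, with exact confidence intervals, the number and proportion with reliable worsening on the MFQ from T1 to T2 and from T1 to T3. The thresholds are a rise above about 0.73 baseline SD for self-report and about 0.88 SD for caregiver report, assuming the German alphas hold in this sample.
- Do the same for caregivers on a BSI scale with a stated reliability, such as depressiveness (about 1.00 SD).
- Base the counts on observed scores. Show patients and caregivers without T2 or T3 data in their own row, and do not rely on imputed values.
- State that these counts, read with adverse events and session ratings, are the evidence for the harm condition in the Discussion.
- For withdrawals, ask the patient or caregiver first, including whether things got worse. Use the therapist only as a fallback and report the source of each reason.
- Reconcile 60% retention with 38 completers, so that the expected denominators are clear.

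The MFQ and BSI counts need analysis wording only, because the scores are already collected. Contact about withdrawals is already foreseen and needs only a change in who is asked first. The downside is small: the intervals will be wide and will make any statement about harm more cautious.
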